# Study protocol for a randomised cross-over trial of *N*eurally adjusted ventilatory *A*ssist for *N*eonates with *C*ongenital diaphragmatic hernias: the NAN-C study

**DOI:** 10.1186/s13063-023-07874-0

**Published:** 2024-01-20

**Keywords:** Neurally adjusted ventilatory assist, NAVA, Congenital diaphragmatic hernia, CDH, Neonatal intensive care, Neonatology

## Abstract

**Background:**

Neurally adjusted ventilatory assist (NAVA) is a mode of mechanical ventilation that delivers oxygen pressures in proportion to electrical signals of the diaphragm. The proportional assistance can be adjusted by the clinician to reduce the patient’s work of breathing. Several case series of infants with congenital diaphragmatic hernias (CDH) have shown that NAVA may reduce oxygenation index and mean airway pressures. To date, no clinical trial has compared NAVA to standard methods of mechanical ventilation for babies with CDH.

**Methods:**

The aim of this dual-centre randomised cross-over trial is to compare post-operative NAVA with assist control ventilation (ACV) for infants with CDH. If eligible, infants will be enrolled for a ventilatory support tolerance trial (VSTT) to assess their suitability for randomisation. If clinically stable during the VSTT, infants will be randomised to receive either NAVA or ACV first in a 1:1 ratio for a 4-h period. The oxygenation index, respiratory severity score and cumulative sedative medication use will be measured.

**Discussion:**

Retrospective studies comparing NAVA to ACV in neonates with congenital diaphragmatic hernia have shown the ventilatory mode may improve respiratory parameters and benefit neonates. To our knowledge, this is the first prospective cross-over trial comparing NAVA to ACV.

**Trial registration:**

NAN-C was prospectively registered on ClinicalTrials.govNCT05839340 Registered on May 2023

**Supplementary Information:**

The online version contains supplementary material available at 10.1186/s13063-023-07874-0.

## Administration information

Note the numbers depicted in braces throughout the protocol refer to *SPIRIT* checklist item number [1]. The order of the items has been modified to group similar items.

## Introduction

### Background and rationale {6a}

Congenital diaphragmatic hernia (CDH) occurs due to an incomplete fusion of the diaphragm during foetal development, enabling abdominal viscera to herniate into the thoracic cavity [2]. Herniation may disrupt development of the lung and associated vasculature, resulting in pulmonary hypoplasia and pulmonary hypertension [3]. Neonates typically undergo surgical reduction in the first few days after birth [4]. The ventilation-perfusion mismatch often seen in infants with CDH can make the post-operative ventilation of this population challenging. The use of mechanical ventilation (MV) is the standard care for babies with CDH in neonatal intensive care units (NICU) across the UK [5]. The use of MV in this patient group, however, can injure the hypoplastic and contralateral lung, termed ventilator-associated lung injury (VALI) [6]. The optimal mode of ventilation to prevent VALI in neonates with CDH remains unclear [4].

One method hypothesised to confer protection to the CDH hypoplastic lung is neurally adjusted ventilatory assist (NAVA). When ventilating with NAVA, a nasogastric tube is passed that contains miniaturised electrodes to detect electrical diaphragmatic signals (Edi). These signals trigger the ventilator to deliver positive pressure at a level, set by the clinician, at the start of inspiration. Inflations are off cycled when the Edi falls by a pre-specified amount [7]. Due to this, NAVA may trigger ventilatory support earlier in the respiratory cycle compared to pressure-triggered ventilatory methods (PTV), where the infant must initiate a sufficient change in pressure or flow to trigger ventilatory support [8]. As a consequence, several small studies have demonstrated that NAVA improves patient-ventilatory asynchrony due to reduced trigger delays and auto or double triggering [9].

In the CDH population, it has been hypothesised that a structurally abnormal diaphragm may impede Edi signal detection and negate the benefits of NAVA. In a retrospective 1:2 matched case-control study, however, there was no significant difference in the Edi signal between infants with CDH ventilated with NAVA and those without [10]. In a retrospective cohort study, five out of seven infants that underwent a surgical patch repair for their CDH had active Edi signals [9]. Several small studies have suggested NAVA is superior compared to assist control ventilation. A retrospective cohort analysis of 15 CDH neonates supported with 72 h of NAVA showed reductions in the peak inspiratory pressure (PIP), mean-airway pressure (MAP) and resulted in less sedative-medication use [11]. Another retrospective cohort of 12 infants in a single centre showed improvements in oxygenation index (OI) on NAVA, compared to pressure-support modes [12].

While results from retrospective analysis have been promising, to our knowledge there has been no prospective crossover trial investigating NAVA for infants with CDH.

### Objectives {7}

Our objective is to determine if for neonates with CDH, NAVA will result in a better OI, compared to ACV. The secondary objective is to determine other clinically important outcomes including sedative medication use.

## Methods

### Trial design {8}

NAN-C is a dual-centre, randomised, open-label cross-over trial designed with a superiority framework. Neither the clinical team nor study investigators can be blinded to the study intervention, but the study statistician will be blinded to each study arm.

### Study setting {9}

This dual-centre randomised cross-over trial will involve two NICUs in the UK. NAN-C was granted a favourable ethical opinion by the West of Scotland Research Ethics Committee (REC).

### Eligibility criteria {10}

We will include neonates (< 28 days of life) with CDH. Eligible Infants will be identified daily by a researcher following discussion with the clinical team. The full inclusion and exclusion criteria can be found outlined in Table 1. Parents of participants meeting all the screening inclusion criteria and none of the screening exclusion criteria will be approached to give consent for their infant’s participation. Post-operatively, infants will then be enrolled within the study and proceed to a ventilatory support tolerance trial (VSTT).

**Table 1 Tab1:** Inclusion and exclusion criteria for participation {10}

Inclusion criteria	Exclusion criteria
▪ Infants born with a congenital diaphragmatic hernia at a gestation age of more than 34 weeks	▪ Known chromosomal anomaly
	▪ Cardiac anomalies expected to require corrective surgery in the first 60 days of birth
	▪ Renal anomalies associated with oligohydramnios
	▪ Skeletal deformities impeding lung or thoracic development
	▪ Severe anomalies of the central nervous system. Including neurological trauma or raised intracranial pressure
	▪ Neuromuscular blocking agent use
	▪ Contraindication to nasogastric tube insertion
	▪ Nitric oxide requirement
	▪ FiO_2_ greater than 80% at the end of the ventilatory support tolerance trial

For the VSTT, neonates will be stabilised for an hour on ACV on the servo-n ventilator (Maquet Critical Care, Solna, Sweden). The positive end-expiratory pressure (PEEP) will be kept 4–5cm H_2_O and inflation time at 0.36–0.4 s. The fraction of inspired oxygen concentration (FiO_2_) will be adjusted with the aim of maintaining oxygen saturations between 85 and 95%. At this stage, infants requiring an FiO_2_ greater than 80% to maintain their oxygen saturation, or requiring nitric oxide, will be excluded.

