### Participant timeline {13}

Screening of participants begins once they have received 24 h of invasive ventilation. Eligible patients will be enrolled into a VSTT. If participants pass the VSTT, they will be randomised to receive either NAVA or ACV first. Participants remain on the assigned ventilator mode for 4 h. Primary outcomes will be recorded for the final 30 min of each ventilation period. Infants will undergo a 20-min stabilisation period prior to receiving the second mode of ventilation for 4 h. There are no follow-up visits of data collection following the total ventilation period (Fig. 1).

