## Interventions

### Intervention description {11a}

A six-French (6 FR) specialised nasogastric tube (EAdi Catheter) is inserted to monitor electromyogram of the crural diaphragm. Correct position of the EAdi catheter is confirmed as per instructions of the manufacturer (Maquet, Servo-n user manual version 4.1) [13]. The guide function displays the retrocardiac echocardiograph. Correct positioning is when the P waves and QRS complexes are visible in the upmost leads and then decrease in size until the P waves disappear in the lowest leads. Coloured highlighting of the central two leads will also appear once the catheter is in the correct place. Once correct positioning is confirmed, the catheter will be securely attached to the infant’s face using an adhesive dressing.

Before infants are changed to NAVA mode (*Servo-n ventilator, Maquet Critical Care, Solna, Sweden*), the NAVA level will be adjusted by the clinician, so the display pressure waveform closely matches the actual pressure waveform, aiming for peak Edi between 5 and 15 microvolts (μV).

On recruitment into the trial, infants will undergo a 1-h VSTT. At King’s College Hospital NHS Foundation Trust infants will be transferred from the SLE 6000 Ventilator (Software versions 4.3; SLE Ltd; South Croydon, UK) to the servo-n ventilator (Maquet Critical Care, Solna, Sweden) for the VSTT. At St. George’s University Hospital NHS Foundation Trust, infants will remain on ACV using the servo-n ventilator (Maquet Critical Care, Solna, Sweden). At this stage, infants requiring an FIO2 of more than 80% to maintain SpO2 85–95%, or requiring nitric oxide infusion, will be excluded.

Infants will then be randomised to receive either ACV or NAVA ventilation modes on the servo-n ventilator for the first 4-h period. All infants will then undergo a 20-min stabilisation period. Following the stabilisation period, infants will then cross-over to receive the alternative ventilatory mode on the servo-n ventilator (Fig. 2)*.*

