**Fig. 2 Fig2:**
[figure not shown]
Ventilation protocol for the NAN-C trial. At King’s College Hospital NHS Foundation Trust (KCH), infants are routinely ventilated using assist control ventilation on the SLE 6000 ventilator. If infants meet the eligibility criteria, they will be transferred from ACV on the SLE 6000 to ACV on the servo-n ventilator (in the above diagram, ventilation machine changes depicted by arrows). Infants will be stabilised on the servo-n ventilator for 1 h in the ventilatory support tolerance trial. If suitable, infants will then be randomised to receive either ACV or neutrally adjusted ventilator assist (NAVA) for 4 h. Following a 20-min stabilisation period, they will then receive the second mode of ventilation. At St. George’s University Hospital (SGH), infants are routinely ventilated on ACV on the servo-n ventilator. Following the VSTT, they will be randomised to either NAVA or ACV on the servo-n ventilator

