## Discussion

Multiple retrospective observational studies comparing NAVA to ACV suggest NAVA may benefit infants with CDH [11, 18–21]. To our knowledge, there has been no prospective trial comparing NAVA to ACV. In this study protocol, we describe a dual-centre, sufficiently powered, randomised cross-over trial needed to determine the most appropriate method of ventilation for infants with CDH.

In the following section, we discuss the rationale for our primary outcome, the definition of the primary outcome, standardisation of the method and other unique aspects of this trial protocol.

Regarding the primary outcome, OI is calculated as MAP × FiO_2_ × 100/PaO_2_ [14]. OI is commonly used to assess the severity of HRF and PPHN of the new-born in NICU. OI is considered a better index than PaO_2_/FiO_2_ ratio as it includes MAP, an important determinant of oxygenation [22]. In infants with CDH, OI is the leading criterion to administer iNO or initiate ECMO [15, 16]. There are several disadvantages to the use of OI in NICU. It requires an indwelling arterial line to obtain a blood gas sample, the sample is dictated by the location of the arterial line and OI can only be intermittently measured when blood gases are taken. We did consider the use of oxygen saturation index (OSI = MAP × FiO_2_ x 100: SpO_2_), which has been shown as a good correlate to OI for infants with HRF [15, 16, 23]. However, due to only one retrospective cohort study of 33 infants with CDH investigating OSI as a correlate for OI, we have decided to utilise OI during this study [16]. NAN-C may be criticised due to a lack of clinical outcomes. Due to a lack of prospective trials investigating OI, MAP and RSS for infants with CDH ventilated with NAVA, we hope our cross-over trial will add to the literature and form a basis for future clinical correlation.

A criticism of previous literature investigating ventilation modes for infants with CDH is the small sample size and single-centre nature of research reflecting the incidence of CDH. Strengths of the study include dual-centre participation.

Lack of familiarity with NAVA may be a study limitation. However, at both centres training will be provided on ventilator modes, and a VSTT is mandatory prior to randomising patients. The mandatory VSTT also safeguards the fidelity of the trial, by ensuring centres can deliver the treatments and record the data according to the proposed methods.

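### The tolerance trial before randomisation tests only ACV, so it does not support the statement that it ensures the treatments can be delivered as far as NAVA is concerned

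*Protocol article*

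**What the plan says.** Eligibility criteria {10} defines the run-in: "For the VSTT, neonates will be stabilised for an hour on ACV on the servo-n ventilator". At its end, infants who need an FiO2 above 80% to hold their saturation, "or requiring nitric oxide, will be excluded".

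The account is the same at both sites. The legend to Fig. 2 says that at the first site "they will be transferred from ACV on the SLE 6000 to ACV on the servo-n ventilator". Intervention description {11a} says that at the second "infants will remain on ACV using the servo-n ventilator".

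Participant timeline {13} makes the run-in the gate to allocation: "If participants pass the VSTT, they will be randomised to receive either NAVA or ACV first".

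The Discussion names unfamiliarity with NAVA as a possible limitation. It answers with training at both centres and with the VSTT: "The mandatory VSTT also safeguards the fidelity of the trial, by ensuring centres can deliver the treatments".

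On the signal that drives NAVA, Background and rationale {6a} reports a retrospective cohort in which "five out of seven infants that underwent a surgical patch repair for their CDH had active Edi signals". Intervention description {11a} describes how catheter position is confirmed, without saying when. It places the adjustment of the NAVA level, with its Edi target, at a stated moment: "Before infants are changed to NAVA mode". The criteria for discontinuing or modifying interventions {11b} exclude an infant who does not trigger the ventilator and name pressure control ventilation as back-up. Statistical methods {20a} and section {20c} call for analysis by intention-to-treat.

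**The concern.** Each infant in a cross-over has to be able to receive both modes. A run-in used to judge suitability for randomisation, and cited as a safeguard for delivering the treatments, should show something about each of them. This one exercises the comparator alone.

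The Background itself raises the worry that a structurally abnormal diaphragm may impede Edi detection. If a missing signal first comes to light after allocation, the infant has already been randomised and there is no usable NAVA measurement to set against ACV. The pair is incomplete, and the loss comes from one mode only. Excluding the infant also conflicts with the stated intention-to-treat analysis, because the reason for exclusion depends on the experimental mode. The same infant, found before randomisation, would be a screen failure and would cost the comparison nothing.

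**Working it through.** **1. What the VSTT tests, set against what is claimed for it.**

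| Element | Part of the VSTT, or required to pass it? | Source |
|---|---|---|
| ACV on the servo-n | Yes, one hour | {10}, {11a}, Fig. 2 legend |
| FiO2 and nitric oxide need | Yes, the only fail criteria | {10}, {11a} |
| Change of ventilator | Yes, first site only | {11a}, Fig. 2 legend |
| Delivery of NAVA | No | – |
| Detectable Edi signal | No | – |
| NAVA level and Edi target | No, set before the switch to NAVA | {11a} |

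The VSTT can show that the machine and ACV work. It gives no evidence on NAVA. Table 1 does not list patch repair as an exclusion, and enrolment is post-operative, so the patch-repaired infants described in the Background can enter.

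**2. The plan's sample size.** Inputs from Sample size {14}: a difference of 1 SD, 80% power, 5% significance, 18 infants. The within-infant correlation rho is not given, and a two-sided paired t-test is assumed. The standardised difference is d = 1/√(2(1 − rho)). At rho = 0, d = 0.707; the noncentral t distribution gives n = 18 with power 80.7%, so the figure is reproduced. It leaves no spare infants: even the 5% loss in {18b} would need 18/0.95 = 18.9, that is 19. The reasons listed there (transfer, withdrawn consent, becoming too unwell) do not include a missing Edi signal.

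**3. The Edi figure.** Without an active signal: 7 − 5 = 2 of 7 = 28.6%. The Clopper-Pearson 95% limits are the 2.5% point of Beta(2, 6) = 0.037 and the 97.5% point of Beta(3, 5) = 0.710.

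**4. Expected number without a signal among 18 randomised.** Formula: 18 × s × p. Here s is the patch-repair share (assumed, as the article gives none) and p is the proportion of patch-repaired infants without a signal. All other infants are assumed to have one.

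| s (assumed) | p = 0.037 | p = 2/7 | p = 0.710 |
|---|---|---|---|
| 30% | 0.2 | 1.5 | 3.8 |
| 50% | 0.3 | 2.6 | 6.4 |
| 70% | 0.5 | 3.6 | 8.9 |

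The chance of at least one such infant is 1 − (1 − s × p)^18. At p = 2/7 it is 80%, 94% and 98% for the three shares. At the low corner (30%, 0.037) it is about 18%.

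**5. Cost in power if pairs are lost.** At rho = 0, power is 78.1% with 17 pairs, 75.3% with 16, 72.2% with 15 and 64.9% with 13. At rho = 0.5, d = 1 and 13 pairs still give 91.1%. The cost in power therefore depends on a correlation that the article does not state.

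**The case against.** The strongest reply has five parts.

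- **Timing of the catheter.** A reader might infer that the signal is first looked for after randomisation, or after four hours of ACV in infants allocated to ACV first. The article does not say so. Only the NAVA-level adjustment is tied to the switch. Catheter insertion and position checking carry no time, and their paragraph precedes the VSTT text. This stands. What remains is that no Edi result is stated as a condition for randomisation, whenever the catheter goes in.
- **Other safeguards.** Table 1 excludes neuromuscular blockade and contraindication to a nasogastric tube, both relevant to NAVA. The Discussion pairs the VSTT with training, and its sentence speaks of centres rather than of each infant's signal. This also stands, so it would be wrong to say that the plan does nothing to prepare for NAVA. None of it makes an hour of ACV evidence that a centre can deliver NAVA.
- **Selection.** A reader might infer that the run-in seriously biases the trial towards infants who do well on ACV. It does not. ACV is routine care at both sites, the criteria are a general oxygenation screen, and the abstract says that infants must be stable during the VSTT. Any effect is modest and mainly on generalisability.
- **Size.** Chances of 80% to 98% of at least one affected infant would be false precision, given the interval around 2/7 and the assumed shares. The Background also cites a matched case-control study with no significant difference in Edi signal. It does not say that NAVA could not be driven in the two infants without an active signal. All of this stands.
- **The count of eighteen.** The article speaks of eighteen infants recruited and places the VSTT on recruitment. The eighteen may therefore be counted before the run-in, in which case an earlier Edi check alone would not protect the number of pairs. This stands and shapes the fix.

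**Conclusion.** The point holds for NAVA delivery, and the plan should be changed. The VSTT is consistently described as one hour of ACV with oxygenation and nitric oxide criteria, so the Discussion claims more for it than it can show. As written, an infant without a usable Edi signal can be randomised and then excluded under {11b}. This leaves no within-infant contrast and sits badly with intention-to-treat.

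The size is uncertain: an expected 0.2 to 8.9 of 18 infants, resting on 2 of 7, assumed patch shares of 30% to 70% and a signal in every infant without a patch. The documents support neither a claim that such losses are nearly certain nor a claim that the trial will be underpowered. The second depends on the unstated correlation.

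**What to change.** - State that a detectable Edi signal is confirmed in every infant before randomisation, and say when the catheter is placed. Any signal threshold is for the investigators.
- Log infants without a detectable signal as screened but not randomised, with the reason.
- Count the eighteen from randomisation, not from recruitment into the VSTT.
- Limit the Discussion sentence to what the VSTT tests: ACV on the servo-n, the change of ventilator at the first site, and data recording.
- Reconcile Eligibility criteria {10}, Intervention description {11a}, the discontinuation criteria {11b} and the Discussion, and say how an infant who still fails to trigger after randomisation is counted under intention-to-treat. The clinical rule itself is for the investigators.

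The cost is small. Every infant is due to receive NAVA and so needs the catheter in any case, and infants who fail to trigger are already removed under {11b}. The check mainly turns a post-allocation exclusion into a screen failure. The price is a few infants screened out, possibly somewhat longer recruitment, and a conclusion stated for infants with a detectable Edi signal.

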### Sample size {14}

The primary outcome is OI. To detect a minimum clinically important difference of one standard deviation with 80% power and 5% significance eighteen infants will be recruited for the trial.

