### Plans to promote participant retention and complete follow-up {18b}

As infants are receiving invasive MV for the duration of the trial, we expect complete follow-up in 95% of randomised patients. We anticipate a 5% loss-to-follow-up rate comprised of infants transferred to other hospitals, consent is withdrawn or become too unwell to participate in the trial.

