### Interim analysis {21b}

We will conduct an interim analysis when nine infants have been recruited. An interim analysis has been planned as previous research investigating NAVA, compared to ACV, for infants with bronchopulmonary dysplasia demonstrated significantly better OI on the former mode of ventilation [16]. To preserve the type I error at 5%, the interim analysis will be conducted at 0.01 with the final analysis conducted using 0.04. This will give an overall type 1 error rate (*significance level*) of 5% [(1–0.01) × (1–0.04) = 0.95 = 1–0.05]. If the interim analysis shows *p* < 0.05, then the trial will stop, and the final analyses will be conducted using patients treated up until that point.

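### The printed 80% power at 5% for eighteen recruited infants matches neither the 0.04 final test nor the number expected to complete, and the SD behind it is undefined

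*Protocol article*

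**What the plan says.** - Protocol article, Sample size {14}: the trial is sized to detect a difference in OI of "one standard deviation with 80% power and 5% significance eighteen infants will be recruited for the trial". No SD value, within-infant correlation or allowance for loss is given.
- Interim analysis {21b}: "the interim analysis will be conducted at 0.01 with the final analysis conducted using 0.04". The interim is triggered when nine infants have been recruited.
- Intervention description {11a}: "On recruitment into the trial, infants will undergo a 1-h VSTT". That section and Eligibility criteria {10} exclude, at this stage, infants above the FiO2 limit or needing nitric oxide. Participant timeline {13} places randomisation after the VSTT is passed.
- Plans to promote participant retention {18b}: "We anticipate a 5% loss-to-follow-up rate", with randomised infants as the denominator.
- Statistical methods {20a}: a t-test or Wilcoxon rank sum test compares the arms. Pairing is not mentioned.
- The Discussion describes the trial as having enough power.

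**The concern.** Four inputs to the power figure are inconsistent or open. The sample size section uses 5%, but the final analysis will be tested at 4%. The eighteen are counted at recruitment, before an exclusion step that precedes randomisation. A 5% loss is expected later, and the sample size section does not mention it. In a cross-over trial, one standard deviation may mean the SD of OI between infants or the SD of the within-infant difference, and these two readings imply very different sample sizes.

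Families, the ethics committee and readers rely on the 80%. If it does not describe the test and the count actually used, a null result is hard to interpret: the trial might have been somewhat short of its target or well above it.

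**Working it through.** **Inputs.** Difference of 1 SD, 80% power, 5% level and 18 infants (Sample size {14}); interim 0.01 at nine infants, final 0.04 (Interim analysis {21b}); 5% loss of randomised infants (retention section {18b}). Sidedness is not stated, so two-sided is assumed. The SD of OI is assumed equal in both periods, with within-infant correlation ρ.

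**Formula.** SD of the within-infant difference = SD × √(2(1−ρ)), so the standardised effect is dz = 1/√(2(1−ρ)). Power of the paired t-test is the probability that a noncentral t with n−1 degrees of freedom and noncentrality λ = dz√n exceeds, in absolute value, the critical t at 1−α/2.

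**Step 1: reproduce eighteen.** With ρ = 0, dz = 0.707.
- n = 18, α = 0.05: λ = 3.00, critical t = 2.110, power 80.7%.
- n = 17, α = 0.05: λ = 2.92, power 78.1%.

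So 18 is the smallest n reaching 80%. It is exactly 18 only for ρ between about −0.015 and 0.045. Two calculations that ignore the pairing also give 18:
- a two-sample t-test at 0.05 needs 17 per period (80.7%), and 17/0.95 = 17.9, rounded up to 18;
- a two-sample t-test at 0.04 with 18 per period has 80.3%.

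If one SD is that of the within-infant difference (dz = 1, the same as ρ = 0.5), 10 infants suffice at 5%.

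**Step 2: use the final level and the expected completers.** 18 × 0.95 = 17.1, so about 17 complete. With ρ = 0 and α = 0.04:
- n = 18: critical t = 2.224, power 77.5%.
- n = 17: critical t = 2.235, power 74.7%.

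Counting rejection at the 0.01 look at nine infants, simulation (400,000 runs) gives overall power of about 78% and 75%. Reaching 80% at the final test with ρ = 0 would take 19 analysed infants.

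**Step 3: vary the correlation** (paired test, α = 0.04, final test alone).

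| ρ | 18 infants | 17 infants |
|---|---|---|
| 0 | 77.5% | 74.7% |
| 0.06 | 80.1% | 77.4% |
| 0.12 | 82.7% | 80.1% |
| 0.3 | 90.4% | 88.4% |
| 0.5, or SD of the difference | 97.2% | 96.3% |

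**Step 4: VSTT exclusions.** No failure rate is given. Purely as an assumed range, 16 or 14 analysed infants at ρ = 0 and 0.04 would have 71.7% or 64.6%. Power would be 80% again at ρ of about 0.18 or 0.30.

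**The case against.** The best defence is that eighteen may already contain what seems to be missing. The two-sample routes in Step 1 reach 18 with the 5% loss included, or at the 0.04 level. A reader might infer that the loss was ignored, or that the number works only at zero correlation. The document supports neither, because the route is not shown. Each of those routes is nevertheless incomplete: the first still uses 5% (with 17 completers the unpaired test at 0.04 has 77.8%), the second contradicts the printed 5% and leaves no room for loss, and both discard the pairing that is the reason for a cross-over.

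A reader might also infer that the trial is underpowered. That does not follow. The two measurements come from the same infant a few hours apart on the same ventilator, and a small positive correlation is enough to restore 80%. The 4% level alone costs about 3 points at ρ = 0, or about 2.5 when the interim look is counted.

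On counting, Table 1 lists the FiO2 result at the end of the VSTT as an exclusion criterion, so the eighteen recruited could mean eighteen who passed. The wording in Intervention description {11a}, which puts recruitment before the VSTT, points the other way. The count is therefore ambiguous, and a proven shortfall in randomised infants cannot be claimed.

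Finally, an article may leave the SD's value and source to the full protocol. That is fair, and their absence is not the point. The point is that the figures printed here do not agree with other sections of the same article.

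**Conclusion.** The point holds as a mismatch between the printed power and the design, not as a demonstrated loss of power. The 80% is stated at 5% for infants recruited, while the plan tests at 0.04 and expects 5% of those randomised to be lost, after VSTT exclusions at an unstated rate. Before any VSTT exclusions, final-test power with 17 completers runs from 74.7% (SD of OI, correlation 0) to 96.3% (SD of the within-infant difference). These figures assume a two-sided paired t-test, normal data and equal SDs in the two periods. The document does not fix which end applies. The undefined SD moves the answer far more than the 4% level does.

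**What to change.** In Sample size {14}, state which SD is meant, preferably that of the within-infant difference in OI, with its value and source. Recompute the power for a paired test at the actual final level (0.04, or its value once the levels and the stopping threshold in Interim analysis {21b} have been reconciled), using the number expected to complete both periods, about 17 of 18, and print that figure.

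Define the eighteen, and the nine that trigger the interim, as infants randomised after passing the VSTT. If VSTT failures are not to be replaced, state the resulting power instead.

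The cost is one recalculation and some rewording. The stated power may become less favourable, and counting after the VSTT may mean consenting a few more infants.
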